### 2.4. Randomization and Blinding

Participants will be randomly assigned to the experimental (SSE training) or control groups. Prior to enrolling participants (1:1) the Research Randomizer software (version 4.0, Geoffrey C. Urbaniak and Scott Plous, Middletown, CT, USA; http://www.randomizer.org, accessed on 23 November 2021) [22] will be used in order to create a randomization sequence. A member of the research team with no active clinical involvement in the trial will conduct this process. Group assignment will be hidden in a password-protected computer file. Participants will be aware of their group assignment, but outcome assessors and data analysts will not know the participants group assignment.

### 2.5. Participants

The participants will be recruited in Cáceres, Extremadura (West region of Spain). To be included in the study, participants will meet the following eligibility criteria: (a) age ≥65 years old; (b) not present or suffer any condition or inconvenience that prevents the normal practice of physical activity; (c) complete and sign the consent form; d) not engage in intense physical activity. The exclusion criterion is (a) presenting or suffering from any neurodegenerative pathology. The participants will be informed about the project via a phone call and meeting. All those who pass the inclusion criteria will be included in the study participation, as shown in Figure 1.

### 2.6. Intervention

#### 2.6.1. Experimental Group

The experimental group will perform the SSE twice a week during a total period of six months. At the start of the intervention, the trainer will state and clarify the training premises. A 200 × 100 cm-thin carpet, divided into 40 squares of 25 × 25 cm, will be used. Training sessions will consist of executing the SSE patterns separated into several mats at once. The SSE is composed by a total of 200 different movement patterns, classified as: beginner, intermediate and advanced [23]. The beginner level will consist of two sub-levels, while intermediate and advanced levels will both have three sub-levels. The intervention will progress through the first six levels up to the advanced level 3. Similarly, participants will start with simple movement patterns (e.g., two-step) and progress to increasingly complex patterns (larger steps per sequence). Table 1 shows the progression of SSE training that will be followed.

Table 2 shows the structure of an SSE training session in the experimental group. Before the beginning of each session, the instructor will show the guidelines to be followed. First, a general and specific warm-up will be performed. Then, the participants will proceed to learn and execute the patterns corresponding to that day; depending on their difficulty, the number of patterns executed will vary between three and five. Once finished, a cool-down consisting of stretching and brief relaxation will be performed to return the body to its initial state. At the end of each training session, a final thought will be conducted where participants will share their opinion on the patterns learned and will rate their perceived intensity of the work performed (from 0 to 10), taking into account the stress and fatigue that has been generated during the training session (Borg Scale) [24,25]. Participants should remain a rate of perceived exertion between 2 and 6.

#### 2.6.2. Control Group

Participators will continue with their typical lifestyle and routine. Once the experimental period is completed, the intervention will be offered to the control participants with no charge.

### 2.7. Outcomes and Procedures

Table 3 summarise several measures that will be taken to assess the utility and effectiveness of SSE program in the cognitive and motor domains (Table 3).

Data collection will take place on 2 days, at baseline, 2, 4 and 6 months, in identical order to avoid alterations. On the first day, blood will be drawn and body composition and risk of falls will be assessed, and on the second day, executive function and physical condition will be assessed. One of the researchers will oversee all measurements except for the blood draw (performed by a skilled worker).

#### 2.7.1. Primary Outcomes

-**Balance**. One leg-stance and four square steps test will be used to asses static and dynamic balance, respectively.
○*One leg stance*. The test consists of standing on one leg for as long as possible (during a maximum lapse of 45 s) while keeping the arms crossed at all times. The test starts when the foot is lifted off the ground and ends when: (1) the arms are uncrossed, (2) the lifted foot touches the ground, (3) when more than 45 s have elapsed. Two variants of this test will be performed, with eyes open (ICC = 0.99) and with eyes closed (ICC = 0.95) [26,27]. Three repetitions of the test shall be performed, and the best time achieved will be recorded.○*Four square steps test (FSST)*. Four squares are formed by placing tape on the floor. At the start of the test, participants standing in the first square in front of square number 2 are asked to walk consecutively (1-2-3-4-4-4-3-2-1) without touching the holes and with both feet in contact with the ground. The time required to complete the full cycle will be recorded (ICC = 0.98) [28].-**Applicability**. All the older people who can undertake the suggested training. If any participant is not capable to perform the intervention, the reason should be mentioned.-**Safety**. In the event of any incident, damage, or trouble during the sessions, a record shall be kept and the source of the incident, injury, or problem noted.

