## Abstract

Background: Age-related changes negatively affect physical fitness, body composition, and executive function and produce a decrease in regucalcin level expression in blood. The square-stepping exercise (SSE) is a balance and lower-limb strength training programme used to prevent falls and stimulate cognitive function in older adults. This project aims to analyse the effects of SSE on executive function, regucalcin expression, fall prevention, body composition, and physical fitness in people over 65 years old. Methods: A randomized controlled trial will be conducted. A total of 90 older people over 65 years old will be recruited and randomly assigned to 2 groups: experimental (*n* = 45) and control (*n* = 45). The experimental group will perform an SSE-based intervention for 6 months (2 times per week), while the control group do not follow any treatment. Results: The main outcome will be balance, but other motor (body mass index, upper- and lower-limb strength, flexibility, and speed-agility) and cognitive variables (executive functions and attention) will be assessed. The expression of regucalcin levels will also be evaluated. Therefore, this project aims to analyse the effect of a 6-month SSE intervention on cognitive and motor competence, physical fitness, regucalcin levels, fall risk, and body composition in older people. If the intervention proves to be effective, it could be implemented in centres, entities, and associations specialized in elderly care.

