### 2.3. Sample Size Calculation

The number of participants to be included in the studies has been calculated based on the change in plasma regucalcin levels, this actual minimum difference being 38.48 AU [21] with a power of 0.65. Hence, a total of 90 participants are required for the studies to be conducted (45 in the experimental group and 45 in the control group), accepting an alpha risk of 0.05. The common standard deviation in regucalcin is assumed to be 192.4 [11] and a loss-to-follow-up rate of 20% has been estimated.

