### 2.8. Statistics

Descriptive statistics and computations will be performed through SPSS (version 25.0; IBM SPSS Inc., Armonk, IL, USA). Data will be presented as means and standard deviation (SD).

Normality and homogeneity of data will be checked applying Kolmogorov–Smirnov and Levene’s tests, respectively. Moreover, an intention-to-treat and a per-protocol analyses will be executed:

**Intention-to-treat analysis**. This analysis will consider all randomly assigned participants in their respective group. Missing data will be input by multiple imputations. Repeated measures ANOVA will be applied to calculate the intervention effects on the different dependent variables, adjusted by age and baseline outcomes. Cohen’s d will be included in results (95% confidence interval) as the effect size. Statistical significance will be computed for the effect of time and the interaction group × time. Alpha level shall be set at *p* ≤ 0.05. Pearson’s bivariate correlations and linear regression will be also computed for analysing the associations between variables.

**Analysis by protocol**. For this analysis, only the volunteers who have completed more than 80% of training sessions will be considered. The same procedures as those indicated for intention-to-treat analysis will be conducted.

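### The main outcome, balance, is three measures each tested at 0.05 with none named as primary; if any one positive is claimed as a balance effect, the false-positive chance is about 11–14%, not 5%

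*Protocol article*

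**What the plan says.** The Abstract of the protocol article states: "The main outcome will be balance". Section 2.7.1 (Primary Outcomes) gives that domain its content: "One leg-stance and four square steps test will be used to asses static and dynamic balance, respectively". For one-leg stance it adds: "Two variants of this test will be performed, with eyes open", and a second variant with eyes closed. With the four square steps test (FSST) that makes three separate timed scores. The section gives no composite, no order among the three and no lead measure.

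On timing, section 2.7 says: "Data collection will take place on 2 days, at baseline, 2, 4 and 6 months". Table 3 schedules balance at all four visits. No month is named as the primary time point.

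Section 2.8 (Statistics) prescribes a repeated measures ANOVA for the dependent variables, adjusted for age and baseline, with significance computed for time and for group × time. The threshold is: "Alpha level shall be set at *p* ≤ 0.05". An intention-to-treat and a per-protocol analysis are both planned, and neither is called primary.

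**The concern.** A main outcome should correspond to one confirmatory test, or to several tests under a rule that holds their joint error. Here it corresponds to three group × time tests, each allowed the full 0.05. If one of the three comes out positive, nothing in the article stops the trial from reporting an effect on balance, and nothing said beforehand which of the three had to be positive. A 5% error rate then no longer describes the headline claim, and the measure carrying that claim can be picked after the results are known.

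The sample size does not settle which measure leads. Section 2.3 bases it on regucalcin, which section 2.7.2 lists as a secondary outcome.

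**Working it through.** **Inputs from the article.** Three balance measures (section 2.7.1). One between-group test per measure, the group × time interaction (section 2.8). Alpha 0.05 for each (section 2.8; section 2.3 also uses 0.05). The time effect is not a between-group comparison and is not counted. The per-protocol repeat is not counted either.

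**Input not in the article.** The correlation between the test statistics of the three measures. It is assumed, over the range 0 to 0.7.

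**The plan's own figure.** The article gives only the 0.05 threshold and no error rate for balance as a whole, so there is no stated overall figure to reproduce.

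**Step 1: independent tests.** The chance of at least one false positive among k tests is 1 − (1 − α)^k. With k = 3 and α = 0.05: 1 − 0.95³ = 1 − 0.8574 = 0.143.

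**Step 2: correlated tests.** Simulation of three two-sided z-tests with equal pairwise correlation (1,000,000 draws):

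| Assumed correlation | Chance of at least one false positive |
|---|---|
| 0 | 14.3% |
| 0.3 | 13.6% |
| 0.5 | 12.5% |
| 0.7 | 10.9% |

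A group × time term over several visits has more than one degree of freedom, so the z-test is an approximation. Repeating the simulation with chi-square tests on 2 or 3 degrees of freedom (400,000 draws) gives 11.1% and 11.3% at correlation 0.7, and 12.7% and 12.9% at 0.5. The range of about 11–14% is unchanged.

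**Step 3: what visit-level testing would add.** The plan does not prescribe this. If each measure were compared separately at months 2, 4 and 6, and any of the nine results could be claimed, nine independent tests would give 1 − 0.95⁹ = 37.0%. Assumed correlations give:

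| Between measures | Between visits | Chance of at least one false positive |
|---|---|---|
| 0.3 | 0.5 | 31.7% |
| 0.5 | 0.6 | 27.8% |
| 0.7 | 0.7 | 22.6% |

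**Step 4: error after the fix.** One named measure with one named test gives 5%. Three tests at 0.05/3 = 0.0167 each give at most 5% (1 − 0.9833³ = 4.9% if independent). Holm starts at the same 0.0167 and also holds 5% overall.

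**Step 5: price of Holm.** Section 2.3 allows 20% loss, so 45 × 0.8 = 36 per arm. For a two-sided, two-sample t-test with 80% power and no covariate adjustment, the detectable standardised difference is 0.67 at α = 0.05 and 0.78 at α = 0.0167.

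**The case against.** The strongest objection is that the article states no rule under which any one positive counts as success. It assigns the two instruments to static and dynamic balance, and if those were reported as two distinct conclusions, a joint error rate over all three tests would not describe either claim. This stands in part: the 11–14% is conditional on a reading that the article leaves open but does not state. It does not remove the point, because the Abstract treats balance as one main outcome and static balance alone already has two measures.

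A second objection is that two of the three measures are variants of the same stance test, so their correlation may well be high. That is fair, and it is why the range extends down to about 11%. Even there the error is more than twice 5%.

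A third is that multiplicity procedures are commonly left to an analysis plan that is not shown. That holds for the adjustment method. It does not hold for which measure is primary, which defines the trial's objective; the article has a primary outcomes section and fixes it without a choice.

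Two stronger readings are tempting and the article does not support them:

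- A reader might infer from the four visits that balance is tested nine times and that the error reaches about 30%. Section 2.8 prescribes one group × time test per measure across all visits, and that test holds its own 5% without a primary month. The higher figures apply only if separate monthly contrasts are added and any may be claimed. Nor is 30% a ceiling, since independence gives 37%.
- A reader might count applicability and safety, which are also listed as primary. They are described as records of reasons and incidents, and they add no hypothesis test.

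**Conclusion.** The point holds as a modest, cheaply corrected weakness. The main outcome is three measures with none in the lead, each tested at the full 0.05. If a positive result on any one is claimed as an effect on balance, the chance of a false claim is about 11–14%, for correlations of 0.7 down to 0 between the three tests. The count of three and the 0.05 come from the article; the correlations and the any-one-positive rule are assumptions. The roughly 23–32% for nine visit-level tests (37% if independent) is a conditional warning about contrasts that the plan does not prescribe, not a property of the plan as written.

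**What to change.** Before any results are seen, adopt one of two options in sections 2.7.1 and 2.8, and update the registry entry to match.

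1. Name one balance measure as the single primary outcome, tested by its intention-to-treat group × time term or by a stated month-6 contrast, and make the other two key secondary outcomes.
2. Keep all three as primary, state that the intention-to-treat group × time tests decide, and apply Holm across them at an overall 0.05.

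In either case, say that contrasts at other months and the per-protocol results are supportive only.

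The work is a few sentences. Option 1 keeps the full 0.05 for the chosen measure but demotes the others, so static or dynamic balance, both deliberately included, loses primary status. If a month-6 contrast is chosen, it also replaces the stated omnibus test as the primary analysis. Option 2 keeps all three but needs a larger effect at the first step: about 0.78 instead of 0.67 SD for 80% power. Those figures assume 36 per arm without adjustment; the planned adjustment for age and baseline, and an intention-to-treat analysis with imputation, would change both.

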Many of the tasks of daily life involve DTs, which are a matter of concern given that because of ageing, older people have problems performing the daily live activities simultaneously. The ability to perform any task may be impaired due to limited attentional resources [15], increased risk of falls [16], loss of independence, and impaired quality of life. Previous studies analysing the effect of DT in older women with fibromyalgia found that gait pattern is affected when an additional cognitive task is added to the primary motor activity; so the walking pattern may be safer and more stable if attention is focused on two simultaneous tasks [17,18]. However, no studies have investigated the impact of DT-based exercise programs on cognitive activity and executive function.

Square stepping exercise (SSE) is a type of physical exercise used in the elderly to reduce the risk of falls [19], but its effects on executive function and regucalcin levels have not been examined. Therefore, this study will analyse the effects of SSE on regucalcin, executive function, physical fitness, balance, fall risk, fear of falling, and body composition in older people. In addition, it will assess the relationship between changes in executive function and regucalcin, physical fitness, balance, fall risk, fear of falling, and body composition in older people.

We hypothesized that (1) SSE will enhance regucalcin levels, executive function, physical fitness, balance, fall risk, fear of falling, and body composition in older people, and (2) changes in executive function and regucalcin will be related to falls, body composition, and physical fitness in older people.

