**Physical Activity levels**. The International Physical Activity Questionnaire (IPAQ) short version will be applied [36]. This questionnaire provides information on the time spent walking, in vigorous and moderate-intensity activity and sedentary activity. The participants will be instructed to refer to all domains of physical activity.

**Fall Risk**. The 21-item Fall Risk Index (FRI-21) will be applied. It is a questionnaire comprising 21 items. Each item is given a rating of 1 (risk) or 0 (no risk), the amount of all items varies from 0 (minimal risk of falls) to 21 (extreme risk of falls). Elevated scores indicate a higher risk of falls. A cut-off point of 9–10 on the FRI-21 is useful for soon identification of falls risk (sensitivity 0.65) [37,38].

**Fear of falling**. The Falls Efficacy Scale-International (FES-I) will be used to measure fear of falling. It is a questionnaire created and authenticated by the Prevention of Falls Network Europe (ProFaNE). It has come to be a tool with excellent accuracy and authenticity for evaluating fear of falling (ICC = 0.96) in different societies and languages, including Spanish. [39,40,41]. The earliest questionnaire includes 16 items and is scored on a 4-point scale (1 = slightly worried to 4 = very worried). Therefore, the best value that can be obtained is 16 and the worst value is 64.

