## 4. Conclusions

This project will investigate the effectiveness of SSE in people over 65 years of age for 6 months with the aim to analyse the effects of SSE on regucalcin, executive function, physical fitness, balance, fall risk, fear of falling, and body composition. Improvements in these variables will mean a reduced risk of developing cancerous tissues and improved performance in activities of daily living. If this intervention proves to be effective, it could be implemented in those centres, entities, and associations specialized in elderly care.

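### Safety is a primary outcome recorded only in SSE sessions, so harms can be described in one arm only; no fall events are counted, so the fall claims reach no further than fall risk and fear of falling

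*Protocol article*

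**What the plan says.** Section 2.7.1 (Primary Outcomes) names three items: balance, applicability and safety. The safety definition is "In the event of any incident, damage, or trouble during the sessions, a record shall be kept", together with a note of the source of the problem.

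Only one arm has sessions. Section 2.6.1: "The experimental group will perform the SSE twice a week during a total period of six months". Section 2.6.2, on controls: "Participators will continue with their typical lifestyle and routine"; they are offered SSE only after the experimental period.

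On falls, the Abstract says the project will "analyse the effects of SSE on executive function, regucalcin expression, fall prevention, body composition, and physical fitness", and hypothesis 2 in the Introduction says "changes in executive function and regucalcin will be related to falls, body composition, and physical fitness in older people". The fall-related instruments in section 2.7.2 are a risk score ("The 21-item Fall Risk Index (FRI-21) will be applied", range 0 to 21) and the FES-I fear-of-falling score (range 16 to 64). Table 3 schedules both, and balance, for both groups at baseline and months 2, 4 and 6.

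Section 4 (Conclusions) states: "Improvements in these variables will mean a reduced risk of developing cancerous tissues and improved performance in activities of daily living". The Discussion makes the same two points only conditionally, as things that improvement could bring or indicate.

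**The concern.** A primary outcome in a randomised trial is expected to be comparable between arms. Section 2.8 analyses all randomised participants in their assigned groups and tests group by time. Safety, as defined, cannot enter that comparison, because its recording window exists in one arm only. If several SSE participants fall or are injured, the trial will have no control rate against which to judge whether training added to the ordinary risk of people aged 65 and over. Events at home, including any delayed consequence of training, are not in the definition for either arm.

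The second issue is what can be said about falls. A lower risk score or less fear is not the same as fewer falls, and the Abstract and hypothesis 2 use words that a reader will take to mean events.

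The third is smaller. The Conclusions announce, as a certainty, a meaning for cancer risk and daily living that the collected data cannot establish.

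**Working it through.** **1. Who can contribute a safety event, and when**

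| | SSE arm | Control arm |
|---|---|---|
| Sessions planned (2 per week × 24 weeks; 2.6.1, Table 1) | 48 | 0 |
| Session length | 40 min (Table 1) or 10 + 40 + 10 = 60 min (Table 2) | none |
| Hours under recording | 48 × 40/60 = 32 to 48 × 60/60 = 48 | 0 |
| Hours in 24 weeks | 24 × 7 × 24 = 4,032 | 4,032 |
| Share covered | 32/4,032 = 0.8% to 48/4,032 = 1.2% | 0% |

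The two tables appear to give different session lengths and need reconciling; the range above covers both. Across the arm, the planned maximum is 45 × 48 = 2,160 person-sessions. That figure assumes full attendance and no loss, and it measures exposure, not bias.

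**2. What the one-arm log can show**

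If no participant had an in-session incident, the one-sided 95% upper limit for the proportion affected would be 1 − 0.05^(1/n). This is 6.4% with n = 45, and 8.0% with n = 36 (45 less the 20% loss assumed in section 2.3). That is a usable statement about tolerability during sessions, but it is not a contrast with control.

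**3. Fall wording set against fall variables**

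- Abstract, opening aim: fall prevention. Abstract, closing aim: fall risk.
- Introduction, aim and hypothesis 1: fall risk and fear of falling. Hypothesis 2: falls.
- Discussion hypothesis and Conclusions list: fall risk and fear of falling.
- Sections 2.7.1 and 2.7.2: FRI-21, FES-I and balance; no count of falls or fallers.
- Table 3: rows for fall risk, fear of falling and balance; none for falls or adverse events. Table 3 also has no row for the IPAQ, which section 2.7.2 does define, so its silence alone would not settle the matter. The outcome definitions show the same gap.

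**4. Would counting falls show a reduction?**

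The protocol gives no fall rate, so this rests on assumptions: 10% to 30% of controls fall at least once in six months, risk ratio 0.5 or 0.7, two-sided alpha 0.05. With p̄ the mean of p₁ and p₂,

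power = Φ{ [ |p₁ − p₂|√n − 1.96√(2p̄(1 − p̄)) ] / √(p₁(1 − p₁) + p₂(1 − p₂)) }.

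| Control risk | Risk ratio | Power, 45 per arm | Power, 36 per arm |
|---|---|---|---|
| 10% | 0.5 | 14.4% | 12.3% |
| 10% | 0.7 | 7.3% | 6.6% |
| 15% | 0.5 | 20.0% | 16.9% |
| 15% | 0.7 | 9.3% | 8.2% |
| 20% | 0.5 | 26.2% | 21.8% |
| 20% | 0.7 | 11.4% | 9.9% |
| 30% | 0.5 | 39.7% | 32.9% |
| 30% | 0.7 | 16.2% | 13.8% |

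Power is about 7% to 40% at 45 per arm, so fall counts would be descriptive.

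**5. Strength of the announced conclusion**

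The Conclusions say that improvement will mean lower cancer risk and better daily living; the Discussion says could. Regucalcin is measured in both arms, but no cancer outcome is. Daily living is reflected only indirectly, through functional tests such as the chair stand, the up-and-go and the walking tests.

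**The case against.** The strongest reply has four parts.

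First, a reader might infer that the trial can make no randomised comparison bearing on falls, or that hypothesis 2 has nothing to be tested on. The documents do not support that. FRI-21, FES-I and balance are measured in both arms at every visit and come under the group-by-time analysis. Most statements of the aim already say fall risk, so the word falls in hypothesis 2 reads naturally as shorthand. What stands is that nothing can be concluded about fall events.

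Second, a reader might infer that a comparative safety conclusion is planned and will fail. None is announced. Safety stands beside Applicability, which also concerns only people doing the training, and together they read as tolerability and feasibility. This is fair, but the item is still placed under Primary Outcomes with a window that only one arm has.

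Third, a journal article may condense a fuller protocol that collects adverse events in both arms. That is possible, and a missing table row alone would be no finding. The session-only window, however, is a stated definition.

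Fourth, counting falls in 90 people would not show a reduction, and self-report may be biased. Both are true (step 4 of the working). They argue for descriptive reporting and for narrower wording. They do not argue against recording events in the same way in both arms.

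**Conclusion.** The point holds in limited form. As written, one of the listed primary outcomes yields information on the SSE arm only. It covers about 1% of that arm's time in the trial and leaves falls and injuries outside sessions uncaptured in either arm. The balance comparison and the other scheduled comparisons are unaffected. Claims about falls can be supported as fall risk and fear of falling, not as falls prevented. The sentence in the Conclusions is stronger than both the data and the Discussion; that is a matter of wording and changes no outcome or analysis.

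No bias in an estimate is claimed, and none can be quantified from the document. The coverage figures assume the planned schedule with full attendance. The power figures rest on assumed fall risks and serve only to show that fall counts would be descriptive at this sample size.

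**What to change.** **Preferred.** At the visits already planned for months 2, 4 and 6, ask every participant in both arms the same questions: falls, injuries and medical contacts since the last visit. Report counts and rates by arm with confidence intervals, labelled descriptive. Keep the session log as a separate, SSE-only measure of tolerability.

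**If no questions are added.** Label Safety as in-session tolerability in the SSE arm, and word the Abstract's aim and hypothesis 2 as fall risk and fear of falling.

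**In either case.** Soften the Conclusions sentence on cancerous tissues and daily living to match the conditional wording of the Discussion.

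**Cost.** A few questions at existing visits, plus edits. Recall over two months will undercount minor falls. The undercount may also differ between arms, because participants know their allocation (section 2.4) and only the SSE arm is seen twice a week. The report should state this limitation.
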